## Abstract

**Background:**

Adherence to pharmacological therapy is a complex and multi-factorial issue that can substantially alter the outcome of treatment. It has been shown that cancer patients, especially when using long-term medication, have similar adherence rates to those of patients with other diseases. The consequences of poor adherence are poor health outcomes and increased health care costs. Only few studies have focused on the use of oral anticancer agents in daily practice. Information about the reasons for non-adherence is essential for the development of interventions that may increase adherence. This paper presents the CAPER-erlotinib protocol, which is designed to study the relationship between adherence to erlotinib and both the plasma concentration and side-effects in patients with NSCLC. Further, the relationships between patient characteristics, disease characteristics, side-effects, quality of life, patient beliefs and attitude towards disease and medication, dose adjustments, reasons for discontinuation and plasma concentration of erlotinib will be explored.

**Methods/Design:**

In this prospective observational cohort study 65 NSCLC patients of 18 years or older starting treatment with erlotinib will be followed for a period up to 16 weeks. The main study parameters are adherence, the plasma concentration of erlotinib and the number and grade of side-effects. At baseline and on erlotinib treatment in weeks 3-4, 8-9, 12 and 15-16, patients will be asked to fill out a questionnaire. In weeks 3-4, 8-9 and 15-16 blood samples are collected, which will be analysed for plasma concentration of erlotinib. Adherence will be measured using a medication event monitoring system.

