### Erlotinib

Erlotinib (Tarceva^®^) is an oral anticancer agent, which is registered for the second- and third-line treatment of NSCLC since 2006 [31] Erlotinib is a tyrosine kinase inhibitor (TKI) of epidermal growth factor receptor (EGFR-TKI).

Diarrhea and skin rash are the most common side-effects of erlotinib. The incidence and severity of diarrhea seems to be related to the schedule and dose of erlotinib [32]. Rudin et al [33] have not observed a relationship between the Area Under the Curve (AUC) concentration and diarrhea. However, they did find a relationship between trough plasma concentration (C_trough_) of erlotinib and skin rash. Hidalgo et al [32] also detected a relationship between AUC and skin rash. Interestingly, patients who experienced skin rash had significantly longer survival [34,35].

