#### Questionnaires

The patients will be asked to fill out five questionnaires spread over 16 weeks. The first questionnaire (t = 0) contains questions on patient characteristics, smoking, co-medication, side-effects, quality of life, and patients beliefs and attitude towards disease and medication. In weeks 3-4, 8-9 and 15-16 patients will be asked to fill out an elaborate questionnaire containing questions determining the adherence behaviour, side-effects, dose adjustment, co-medication, quality of life, and patients beliefs and attitude towards disease and medication. In week 12 patients are asked to fill out a short questionnaire containing only questions determining the adherence behaviour, side effects, and dose adjustment. Discontinuation and reasons for discontinuation will be asked in a short questionnaire when a patient stops the erlotinib treatment prematurely.

The questionnaires contain the following items:

1. MARS (Medication Adherence Report Scale) [40,41]. This questionnaire contains statements about adherence behaviour.

2. Nature and grade of the side-effects in a five-point scale.

3. Quality of life measured with SF-12 Health Survey [42,43]. The SF-12 is a short version of the SF-36 and is a validated method to measure quality of life.

4. Attitude towards disease measured with Brief Illness Perception Questionnaire (Brief IPQ) [21]. The Brief IPQ is a validated method to measure the attitude towards disease.

5. Beliefs and attitude towards medicines measured with Beliefs about Medicines Questionnaire (BMQ) [22]. The BMQ is a validated questionnaire. It is divided in two parts, the BMQ general and the BMQ specific. BMQ general measures the patient's beliefs and attitude towards medicines in general. The BMQ specific is specified for erlotinib.

6. Patient characteristics: date of birth, gender, socio-economic status and smoking (current smoking and never/previous smoking).

7. Dose adjustments by the patient. Dose adjustments introduced by the doctor will be derived from the patient file.

8. Co-medication.

9. Discontinuation and reasons for discontinuation. Discontinuation is also derived from the patient file.

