### Statistics

The data will be described by means of frequency analysis. Correlation coefficients will be calculated for relationships between adherence, patient characteristics, disease characteristics, side effects, quality of life, patient beliefs and attitude towards disease and medication, dose adjustments and plasma concentration of erlotinib in patients with NSCLC. In particular, the correlation coefficient between plasma concentration and side-effects; the relationship between dose and plasma concentration in daily practice; the influence of different factors on adherence; the influence of different factors on side-effects; the influence of different factors on quality of life; the influence of different factors on dose adjustment and discontinuation. By the use of a multivariate regression analysis the influence of adherence (dependent variable) on plasma concentration and the influence of side-effects (dependent variable) on adherence will be calculated. The dependent variables will be adjusted for potential confounders. For all analyses a two-tailed significance level will be 0.05, all p values below this level will be considered statistically significant. The statistical analyses will be performed with SPSS 15.0 (SPSS Inc. Chicago, Illinois, USA).

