## Discussion

The present study aims to get more insight into patients' experiences with the use of erlotinib in daily practice. We expect variability in the adherence in the general oncology population. This may be complicated by the inter-patient variability in the pharmacokinetics. We hypothesize that side-effects play an important role in the way patients use erlotinib. Therefore, the relationship between self-reported side-effects and adherence is also defined as a main objective. To get more insight into other factors related to adherence and other aspects of the use at home, the effects of determinants are studied in an explorative manner.

We expect that the present study will provide valuable knowledge on patients' experiences with the use of erlotinib. This knowledge will be useful for health care professionals to develop specific interventions to support patients thus improving the adherence and persistence with the use of erlotinib in order to derive optimal benefit from the medication.

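### Side-effects are asked at t = 0, but the analyses of on-treatment side-effects give that baseline score no stated role

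*Protocol article*

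**What the plan says.** The abstract of the protocol article (Methods/Design) names the main variables: "The main study parameters are adherence, the plasma concentration of erlotinib and the number and grade of side-effects". The Discussion confirms that "the relationship between self-reported side-effects and adherence is also defined as a main objective".

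The schedule separates baseline from treatment: "At baseline and on erlotinib treatment in weeks 3-4, 8-9, 12 and 15-16, patients will be asked to fill out a questionnaire". Under Questionnaires, side-effects are among the items at both stages. For baseline: "The first questionnaire (t = 0) contains questions on patient characteristics, smoking, co-medication, side-effects, quality of life". The instrument is described only as "Nature and grade of the side-effects in a five-point scale".

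The Statistics section plans correlation coefficients among the study variables and singles out the one between plasma concentration and side-effects. It then plans a multivariate regression in which "the influence of side-effects (dependent variable) on adherence will be calculated", followed by one general sentence: "The dependent variables will be adjusted for potential confounders". The confounders are not listed. No section gives the t = 0 side-effect score a use, whether as covariate, change score or reference for new or worsened complaints.

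**The concern.** The patients have advanced NSCLC, and the article describes erlotinib as "registered for the second- and third-line treatment of NSCLC since 2006". Some will plausibly start with complaints from the disease or from previous therapy, although the article does not say how many. Asking about side-effects before treatment makes sense only if such complaints are expected.

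The working hypothesis is that side-effects of erlotinib influence how patients use it. If the on-treatment score is analysed without its baseline, it mixes two things: what was there before and what came with erlotinib. If the pre-existing part is unrelated to adherence, it is noise and weakens the correlation. If it is related to adherence for other reasons, for example because sicker patients take their tablets differently, it can hide or exaggerate the relation. The same holds for plasma concentration: a complaint that predates the first dose cannot have been caused by the erlotinib level.

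**Working it through.** **Baseline score against each planned analysis**

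| Analysis | Stated adjustment | t = 0 score named? |
|---|---|---|
| Correlation, side-effects with adherence | none | no |
| Correlation, plasma concentration with side-effects | none | no |
| Regression, side-effects as dependent variable | unlisted potential confounders | neither named nor excluded |

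**Plan's own figure.** The only number is 65 patients. The article shows no effect size or power, so there is no calculation to reproduce. For scale, the Fisher z formula gives the correlation that 65 patients detect with 80% power at two-sided 0.05:

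r = tanh((1.960 + 0.842)/√62) = 0.34.

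**Illustration: inputs.** From the article: n = 65 and two-sided alpha 0.05. Assumed, not in the article: treatment-emergent burden E correlates -0.35 with adherence; pre-existing burden B is independent of E and has v times its variance; a fraction c of each baseline score persists, so the on-treatment score is cB + E; B correlates b with adherence. All 65 patients are taken to contribute.

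**Formulas**

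- Raw correlation: r = (-0.35 + b·c·√v) / √(1 + c²v)
- Power: Φ(atanh|r|·√62 - 1.960)
- No carry-over: atanh(0.35) = 0.365; 0.365 × 7.874 - 1.960 = 0.917; power 82%.

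**Dilution (b = 0)**

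| v | r, full persistence (c = 1) | power | r, half persistence (c = 0.5) | power |
|---|---|---|---|---|
| 0.5 | -0.29 | 64% | -0.33 | 77% |
| 1 | -0.25 | 51% | -0.31 | 72% |
| 2 | -0.20 | 36% | -0.29 | 64% |

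The row v = 1 with c = 1 is the case in which half of the score variance is carried over: -0.35/√2 = -0.247.

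**Bias (c = 1, true value -0.35)**

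| v | r if b = +0.2 | r if b = -0.2 |
|---|---|---|
| 0.5 | -0.17 | -0.40 |
| 1 | -0.11 | -0.39 |
| 2 | -0.04 | -0.37 |

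For v = 1: (-0.35 + 0.20)/1.414 = -0.11 and (-0.35 - 0.20)/1.414 = -0.39.

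**With the t = 0 score partialled out.** Removing B from the on-treatment score leaves E for any c. The partial correlation is -0.35/√(1 - b²), which is -0.35 for b = 0 and -0.36 for b = ±0.2. Replacing √62 by √61 for the lost degree of freedom, power at b = 0 is 81%, against 82% without carry-over.

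**The case against.** The strongest reply is that this rests on silence in a condensed article. The Statistics section does promise adjustment for potential confounders. In that regression side-effects are the dependent variable, so the t = 0 score is an obvious candidate. Covariate lists are often left to the analysis plan, and collecting the items at baseline suggests that a comparison was intended. Disease stage and line of treatment, taken from the patient file, would also carry part of the pre-existing burden.

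Much of this stands. A reader might infer that the plan discards the t = 0 score, or that it scores every persisting complaint as an erlotinib side-effect. The article supports neither: it contains no such scoring rule, does not exclude the baseline score from adjustment, and does not show the item wording, so patients may be asked to attribute complaints to erlotinib.

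The general adjustment sentence still does not settle the point. It concerns the dependent variables of the regression and leaves the correlations untouched. Pre-existing burden that is unrelated to adherence is not a confounder, so a confounder rule need not bring it in, yet it still dilutes. And the article does name covariates for the pharmacokinetic model, under Blood sample and laboratory test, while saying nothing about the one baseline measurement that matches its side-effect parameter.

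Two further objections limit the point. The illustration assumes no reporting error and a model that suits the adjusted analysis. And if patients act on their total perceived burden, that total is a legitimate quantity, so redefining the main parameter as new-or-worsened complaints would change the question.

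**Conclusion.** The concern holds as an unstated use of data already collected. Following the text as written, complaints that predate erlotinib can enter a main parameter and can dilute or bias its relation with adherence and with plasma concentration.

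The size is unknown. The figure of 51% power instead of 82% requires a true correlation of -0.35, full persistence and half of the score variance carried over; with half persistence and the same baseline variance, power is 72%. The direction of any bias is not established either. The documents give none of these inputs, so the numbers show only that the effect could matter with 65 patients, not that it will.

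**What to change.** In the Statistics section, state that the t = 0 side-effect score is a covariate in every regression of on-treatment side-effects. For side-effects with adherence and for side-effects with plasma concentration, use partial correlations adjusted for the t = 0 score.

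Keep the main parameter as it is. Report two sensitivity analyses: one counting only items that are new or worse than at t = 0, and one for skin rash and diarrhoea separately, which the Erlotinib section names as the most common side-effects. Do not combine the new-or-worse count with the covariate in the main analysis.

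The cost is a few lines of analysis text, one degree of freedom per model, and a stated rule for patients without a t = 0 form, who would otherwise drop out of the adjusted analyses. No new data are needed.

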**Discussion:**

The present study aims to get more insight into patients' experiences with the use of erlotinib in daily practice and the various aspects that govern adherence. We hypothesize that side-effects play an important role in the way patients use erlotinib. We expect that the present study will provide valuable knowledge which will be useful for health care professionals to develop interventions to support patients. This approach will improve the adherence and persistence with the use of erlotinib in order to derive optimal benefit from the medication.

**Trial Registration:**

NTR1830

## Background

In the pharmacological treatment of cancer intravenous (IV) therapy has played an important role. Since the last decade a growing number of oral substances has been introduced in cancer treatment. Most patients prefer oral use of anticancer agents as long as it does not compromise the outcome of treatment [1,2]. In addition, the overall costs of oral treatment are often lower than those of IV therapy [3-5]. However, with the use of oral medication at home in daily practice the issue of adherence needs to be considered.

### Adherence

Adherence to oral pharmacological therapy is a complex and multifactorial issue that can substantially alter the outcome of therapy [6,7]. Adherence (synonymous with compliance) has recently been defined by the International Society for Pharmacoeconomics and Outcome Research (ISPOR) as the extent to which a patient acts in accordance with the prescribed interval and dose of a dosing regimen [8]. A patient is optimally adherent if no doses are missed, no extra doses are taken, and no doses are taken in the wrong quantity or at the wrong time. Adherence is measured over a period of time and reported as the adherence rate, which is the percentage of dose taken in relation to what was prescribed [9]. There are several methods to measure adherence, including self reports, pill counts, electronic monitoring systems, analyses of pharmacy dispensing databases or assessment of blood or urine samples. There is no golden standard measurement and all methods have limitations [9,10]. The major limitation of measuring adherence is the so called Hawthorne effect: the measuring of adherence itself influences the adherence because the awareness of patients that adherence is being measured may influence their behaviour. Adherence rates for many chronic drug therapies have been shown to range between 35-70% [11]. The consequences of poor adherence are poor health outcomes and increased health care costs [6].

### Adherence in oncology

Cancer patients are generally thought to have higher adherence rates than other patients because they are highly motivated by the gravity of their disease [12,13]. However, it has been shown that cancer patients have similar adherence rates to those of patients with other diseases [9,14,15]. Treatment duration plays a role in the adherence to the regimen. When the medication is continued over a longer period of time, patients become less adherent [16].

In oncology adherence has been studied mainly in two subpopulations, both using long-term medication. In the first population, breast cancer patients on adjuvant hormonal therapy like tamoxifen the adherence rate has been subject of several studies [9]. The reported adherence rates range from 50% to 98% [13,16,17]. Several studies concerning adherence to oral medication have been published in the second subpopulation, patients with Chronic Myeloid Leukemia (CML) [15,18,19]. Non adherence appear to be associated with poorer response to imatinib [15,18]. Noens et al have shown that patients with suboptimal response had higher percentages of imatinib not taken (23%) than those with optimal response (7%). Marin et al have demonstrated in CML that there was a strong correlation between adherence rate and response. Adherence was the only critical factor for achieving molecular response.

Another frequently overlooked problem is over-adherence. This may be more an issue in oncology patients than in other patients and may, in the case of oral anticancer agents, lead to substantially increased toxicity [10]. In the study by Nilsson et al. [14], 30% had an oversupply of their medication.

Oncologists may not always consider the issue of adherence. Yet, suboptimal adherence may prove to be the greatest barrier to the effective use of new oral agents [9,18].

### Causes of non-adherence

Several factors have shown to be associated with non-adherence. These include patient variables like demographic factors, patients beliefs, disease variables, various aspects of treatment regimes, side- effects and quality of life.

The common sense model of self-regulation (CSM) developed by Leventhal et al [20] is a commonly used theoretical model to understand patients perceptions of illness. According to the CSM peoples' perception of and beliefs about their illness is an important factor in their reactions and behaviour to health threats. Illness perceptions can easily be measured with the Brief Illness Perceptions Questionnaire (Brief IPQ) [21].

Another factor which may influence adherence is patients beliefs about the medication. These representations are usually determined with the Beliefs about Medicine Questionnaire (BMQ) [22]. Associations between adherence and BMQ scores have been shown[23-27].

Few studies have focused on patients' reasons for not adhering to oral anticancer agents. Eliasson et al [28] have reported that finding ways to deal with the side-effects leads to better adherence in patients with CML. In clinical trials adverse events are generally reported by clinicians, e.g. the National Cancer Institute's Common Terminology Criteria for Adverse Events (CTCAE). Basch et al have shown the value of patients' reported adverse symptom events in cancer patients, which better reflect their daily health status [29,30].

### Erlotinib

Erlotinib (Tarceva^®^) is an oral anticancer agent, which is registered for the second- and third-line treatment of NSCLC since 2006 [31] Erlotinib is a tyrosine kinase inhibitor (TKI) of epidermal growth factor receptor (EGFR-TKI).

Diarrhea and skin rash are the most common side-effects of erlotinib. The incidence and severity of diarrhea seems to be related to the schedule and dose of erlotinib [32]. Rudin et al [33] have not observed a relationship between the Area Under the Curve (AUC) concentration and diarrhea. However, they did find a relationship between trough plasma concentration (C_trough_) of erlotinib and skin rash. Hidalgo et al [32] also detected a relationship between AUC and skin rash. Interestingly, patients who experienced skin rash had significantly longer survival [34,35].

### Pharmacokinetics

Hidalgo et al [32] have suggested that an erlotinib plasma concentration of 0.5 μg/ml would be sufficient for relevant antiproliferative activity. Peak concentrations (Cmax) of erlotinib of 1.737 ± 0.777 μg/ml are reached 2.44 ± 1.94 hour (Tmax) after administration of 150 mg a day. Erlotinib has a plasma volume of 233 L and is for 95% bound to plasma proteins like albumine and α1-acid-glycoprotein. The plasma elimination half-life is approximately 36 hours [36]. Erlotinib is mainly metabolized by the liver (90%), only a small part is excreted by the kidneys (9%). It is primarily metabolized by cytochrome P450 3A4 (CYP3A4) and in a lesser extent by CYP1A2, It is a substrate of the multi-drug transporter ATP-binding cassette transporter ABCG2 [37].

Several drug interactions, smoking and food may influence plasma concentrations of erlotinib. Drugs that increase the pH of the upper gastrointestinal tract may alter the solubility of erlotinib, thereby reducing its bioavailability. Inhibitors or inducers of CYP3A4 and CYP1A2 influence the metabolism of erlotinib, which may result in increased or decreased plasma concentrations [31] Smoking results in a significantly lower plasma concentration [38]. When erlotinib is taken together with food the bioavailability of erlotinib increases almost two-fold [39]. It is therefore advised by the manufacturer to take erlotinib at least one hour before or two hours after a meal [31]. Serum total bilirubin, serum α1-acid glycoprotein, serum albumin, creatinine clearance and gender are significant co-variables that explain interindividual variability for clearance [36].

### Objectives

The primary objective is to get insight into the relationship between adherence to erlotinib and the plasma concentration of erlotinib and the relationship between adherence and side-effects in patients with NSCLC. Furthermore, the relationships between patient characteristics, disease characteristics, side-effects, quality of life, patient beliefs and attitude towards disease and medication, adherence, dose adjustments and plasma concentration of erlotinib in patients with NSCLC will be explored.

